### Primary outcome

For the primary outcome, that is, child attachment security (vs. insecurity) as a categorical variable, differences of the proportions of child attachment security between TAU and COS treatment arms will be estimated by a chi-square test of statistical significance.

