### Interventions

This trial aims to evaluate the efficacy of the COS group treatment protocol compared to TAU as the control condition. The COS group intervention consisted of 20 90-minute sessions delivered weekly on Tuesday afternoons, plus one additional session of 120 minutes with the fathers or close family members on one Saturday. The TAU condition was delivered at different levels of intensity, as needed by the mothers. Mothers assigned to either of the treatment arms were permitted to receive psychopharmacological medication as part of their adult psychiatric treatment to manage clinical symptoms, as well as individual psychotherapy and/or other psychosocial services.

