[71,72], which represents the emotional organization of relationships and the basis for defensive processes in the parent–child interaction. The need for relationships and the fear of the loss of these relationships or separation play central roles in this. Each mother’s idiosyncratic manifestation of this complex interplay was taken into consideration in the selection of the video sequences.

Every therapeutic group consisted of six women. Six groups were planned and realized for this trial. The infants did not participate in group sessions, and childcare was provided for them while the mothers were in sessions.

The treatment manual, which was designed for parents with children aged 0–5 years, combines psycho-educational and therapeutic modules (e.g., video analyses in the group), focusing on attachment, exploration, communication and affective experiences between parent (in this study, mother) and child, aiming to help the mothers to elaborate their strengths and struggles in order to create a haven of safety and a secure base for their children. Guided by the treatment manual, there is a shift from predominantly observing behavioral and affective cues of both mother and child to gaining more insight into maternal thoughts and feelings and their defensive nature (“shark music”) with regard to the attachment and autonomy needs of the children, with the goal of overcoming their impact on child-mother attachment formation and maternal sensitivity. This is intensified by showing video segments of the “linchpin struggle” of each mother-infant dyad.

The 90-minute-COS group sessions took place weekly. Two therapists facilitated each group. Treatment adherence and integrity in this study was assured by weekly supervision of the therapists with [name], one of the originators of the COS intervention.

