#### *Treatment* a*s usual (TAU)*

As a control condition, TAU was provided to mothers with their infants within the child and adolescent psychiatric outpatient unit. TAU consisted of standard treatment, which may have involved case management or counseling for the mothers. The treatment was offered by two child and adolescent psychiatrists and psychotherapists with a theoretical blend of psychodynamic and behavioral training in therapeutic work with mentally disordered mothers and infants. The focus was on the mother, the child, and/or the mother–child relationship; fathers were sometimes included. Each treatment session typically lasted 50 minutes. The intensity and length of treatment depended on the specific needs of each mother–infant dyad, and treatment was terminated by the mothers. The exact number of treatment sessions was recorded. Mother–infant dyads with particular needs were referred for additional services (e.g., social support services, family midwives). Most of the mothers attending the outpatient unit had seen an adult psychiatrist to confirm their diagnosis and further treatment indications at least once, at the beginning of treatment. At the time of follow-up, treatment satisfaction will be assessed for all mothers in the COS and TAU groups.

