**Figure 1 F1:**
[figure not shown]
Consort diagram describing flow of patients through study.

Identification and initial screening of potential participants were performed by the principle investigator of the study, an experienced clinician in the outpatient unit. Once eligible mother-infant dyads were identified, they were informed about the trial and invited to participate. Both custodial parents had to give their informed consent for the baseline assessment, which was performed by trained research staff over several sessions. After completion, the researcher confirmed whether each mother met diagnostic and additional inclusion criteria. If they did, they were randomly assigned to one of the two treatment arms (COS or TAU). Once consent to treatment and post-assessment of both parents had been obtained, a trial ID was assigned. Depending on the natural flow of patients a COS group began once six mother-infant cases had been recruited and assigned. TAU started immediately after random allocation. Follow-up assessment (child age 16–18 months) is continuing.

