### Limitations

The circumstances of this clinical trial necessitated some scientific compromises. One limitation of this trial is that the person who oversaw the implementation of the COS intervention is also the principle investigator. Thus, personal factors (allegiance effects) may limit the generalizability of our findings. In view of the fact that the study sample comprises clinically referred mothers with mental disorders and their infants, it is ethically unacceptable to use a no-treatment control group. Therefore, in the best interest of our patients we have used TAU as the control intervention to which patients are randomized. According to the natural flow of patients attending the outpatient unit, eligible women with infants participated voluntarily, and, having given their informed consent, were randomly assigned to COS or TAU. Thus, our clinical sample varied in terms of psychopathology. There may be a sampling bias, insofar as the mothers with infants attending the outpatient unit might represent a more severely mentally disordered sample choosing to participate in this trial. This may limit the generalizability of the findings, due to sampling bias and a lack of true representativeness. Hence, replication studies or a multi-site trial are necessary. A sample size of N = 80 was determined before any data were collected, based on the assumption of medium effect size and power. For practical reasons, we defined a sample size of N = 72, such that 36 mother-infant dyads were randomly assigned to COS (six COS therapeutic groups) and 36 mother-infant dyads to TAU. Further long-term follow-up measures might be useful to capture positive changes of the intervention that may be attributable to a sleeper-effect
[66] and apparent only at later follow-up stages.

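### COS is given in six therapy groups of six, but the primary chi-square treats COS dyads as independent, so its type I error exceeds 5% if outcomes correlate within groups

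*Protocol article*

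**What the plan says.** The section on the COS intervention describes a group treatment: "Every therapeutic group consisted of six women", "Two therapists facilitated each group" and "Six groups were planned and realized for this trial". Under Interventions, "The COS group intervention consisted of 20 90-minute sessions delivered weekly on Tuesday afternoons". Under Recruitment and baseline procedures, "a COS group began once six mother-infant cases had been recruited and assigned", so groups were filled in order of recruitment, after individual 1:1 randomization. Limitations gives the numbers as run: "36 mother-infant dyads were randomly assigned to COS (six COS therapeutic groups) and 36 mother-infant dyads to TAU".

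TAU is described differently. "The treatment was offered by two child and adolescent psychiatrists and psychotherapists", with length and intensity set by each dyad's needs, and no therapy group is mentioned.

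The primary analysis is fixed in one sentence: "differences of the proportions of child attachment security between TAU and COS treatment arms will be estimated by a chi-square test of statistical significance". The sample size of 80 rests on the same test. None of the secondary analyses a to h includes a group term. Limitations mentions the six groups but not clustering.

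**The concern.** This is an individually randomized trial with clustering in one arm only. Mothers in a COS group share 20 weekly sessions, facilitators and a calendar period, so outcomes within a group may be more alike than outcomes across groups. A two-by-two chi-square assumes that all 72 dyads are independent. With positive within-group correlation, it understates the variance of the COS proportion. An unusually good or poor group can then pass for a treatment effect.

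The same holds for the secondary analyses that include treatment arm: a and b (repeated-measures ANCOVA), c and f (linear regression), and d and h (logistic regression).

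This is not a detail left to an unseen analysis plan. The article names the primary test, and that test has no place for a group effect.

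**Working it through.** **Inputs from the article.** Six COS groups of six; 36 COS and 36 TAU dyads as run; planned N = 80; W = 0.3; alpha 5%; power 80%.

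**Assumed.** ICC within COS groups of 0 to 0.20 (none is given); TAU dyads independent; a two-sided test; a secure rate of 0.3 to 0.5 under the null; complete follow-up.

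**1. The plan's own figure.** A two-sided chi-square with 1 df and noncentrality N × 0.3² needs N = 87.2, so 88, for 80% power. Power is 76.5% at N = 80 and 72.1% at N = 72. The stated 80 does not reproduce on this reading. That is a separate matter; the 72% is the baseline used below.

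**2. Variance.** The COS design effect is 1 + (6 − 1) × ICC and the TAU design effect is 1. With equal arms, the variance of the difference is multiplied by [(1 + 5 × ICC) + 1] / 2 = 1 + 2.5 × ICC. The effective COS sample size is 36 / (1 + 5 × ICC).

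**3. Type I error.** Approximate two-sided alpha = 2 × [1 − Φ(1.96 / √(1 + 2.5 × ICC))]. At ICC 0.10, for example, √1.25 = 1.118, 1.96 / 1.118 = 1.753, and alpha = 8.0%. A beta-binomial simulation (400,000 runs, six groups of six against 36 independent dyads) checks this for the uncorrected test. A second one (200,000 runs) covers the continuity-corrected test. Ranges run over secure rates of 0.3 to 0.5.

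| ICC | Variance factor | Effective COS n | Alpha, formula | Uncorrected, simulated | Continuity-corrected, simulated |
|---|---|---|---|---|---|
| 0 | 1.000 | 36 | 5.0% | 4.5-5.3% | 2.5-2.8% |
| 0.02 | 1.050 | 33 | 5.6% | 5.2-5.9% | not reported |
| 0.05 | 1.125 | 29 | 6.5% | 5.9-6.8% | 3.4-3.8% |
| 0.10 | 1.250 | 24 | 8.0% | 7.6-8.3% | 4.6-4.9% |
| 0.20 | 1.500 | 18 | about 11% | 10.6-11.5% | 6.9-7.3% |

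**4. Does a remedy work with only six groups?** Take the mean of the six COS group proportions minus the TAU proportion. Its variance is v1 + v2, where v1 = (variance of the group proportions) / 6 and v2 = (TAU sample variance) / 36. The Satterthwaite df are (v1 + v2)² / (v1²/5 + v2²/35). Simulated type I error is 5.1-6.0% for ICC 0 to 0.20.

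**5. Power of that remedy.** With 0.65 against 0.35, W = 0.30 / (2 × √(0.5 × 0.5)) = 0.3. At 36 per arm, power is about 69% at ICC 0, 63% at 0.05 and 58% at 0.10. Applying the variance factor without the small-sample df gives 67% and 62% at ICC 0.05 and 0.10, which is too optimistic.

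**The case against.** The strongest reply is that nothing in the article shows a positive ICC. The infants, whose attachment is the outcome, did not attend the sessions, and each dyad had its own treatment plan. Both could weaken group correlation. At ICC 0.02 or below the excess is negligible. The article does not say whether a continuity correction applies; with one, the error stays under 5% up to ICC 0.10. All of this stands and limits the size of the point. It does not make independence a safe assumption for a treatment delivered in groups.

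Individual randomization also protects the test when COS has no effect on anyone. That stands too. The inflation belongs to the case where group results vary around a zero average, which matters for any claim about COS beyond these six groups.

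A reader might infer more than the text supports:
- That the error rate is certainly too high. This depends on the ICC and on the form of the test.
- That every secondary p-value is affected. Analysis e correlates change scores, and g lists only maternal changes as predictors; neither names an arm comparison.
- That the groups were closed, or that therapist pairs differed between groups. Neither is stated. If one pair led all six groups, its effect is confounded with arm, and a group term would not remove it.

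Finally, TAU dyads may correlate within the two TAU clinicians. Assuming 18 dyads each and ICC 0.05 in both arms, the variance factor is (1.25 + 1.85) / 2 = 1.55 and alpha is about 11.5%. Treating TAU dyads as independent is therefore itself an assumption.

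**Conclusion.** The point holds in conditional form. The plan analyses a partially nested design as independent data, in the primary test and in secondary analyses a, b, c, d, f and h. If outcomes correlate within COS groups, the evidence for a treatment difference is overstated. For an uncorrected test the excess is slight at ICC 0.02 and material from about 0.05 upward, reaching roughly twice the nominal 5% at 0.20. These figures rest on an assumed ICC, full groups of six and no clustering in TAU; smaller groups at follow-up would reduce the inflation.

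This should be fixed. The documents do not support calling the primary result invalid, because the ICC is unknown and the test is sound if COS has no effect on anyone.

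**What to change.** Before the primary analysis, replace the chi-square as the primary method with one that respects the grouping in COS. Two workable forms for the binary outcome are:
- a risk difference from COS group means against individual TAU dyads, with Satterthwaite df;
- a linear probability mixed model with a random group effect in the COS arm only and the same type of df correction. This copes more easily with unequal groups after dropout.

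Name the model scale explicitly, because Satterthwaite df belong to linear models and do not carry over to a logistic mixed model. Report the risk difference with its 95% CI and the estimated ICC. Keep the chi-square as a sensitivity analysis and state whether it is continuity-corrected. Use the same nesting structure in secondary analyses a, b, c, d, f and h. State that TAU dyads are treated as independent despite sharing two clinicians.

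The cost is plan wording and analysis work. Group membership follows from the design, and the article describes follow-up as still under way, so conduct need not change. The interval will be wider and its group variance will rest on six groups. Even if the ICC is zero, power at W = 0.3 and N = 72 falls from 72% to about 69%.

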#### Randomization procedures and methods to minimize bias

Eligible patients were randomly assigned to the COS intervention or TAU in a ratio of 1:1. An electronic randomization list was generated using Randlist 1.2 as a random generator. Unique randomization numbers were generated to ensure that the study arm assignment was unbiased. Randomization was stratified for two infant age groups (4–6 months vs. 7–9 months) and separate random lists were created for each age group. Block sizes of six to eight were used for the randomization of the treatment arms. The randomization list was generated by the randomization representative and was stored in a password-protected electronic document accessible only by the randomization representative. Each random number was stored in a concealed randomization envelope. After a patient’s eligibility for the study was determined, the next available randomization number was assigned to the patient, in ascending order. To minimize bias that could have arisen from knowledge of treatment allocation, all outcome assessors were blind to treatment allocation and a random sample of outcome measures was re-rated by independent assessors.

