### Statistical methods

#### Sample size and power

The primary outcome for treatment efficacy is the rating of quality of child attachment at follow-up at children’s age 16–18 months (COS vs. TAU) by an objective rater blind to treatment allocation. Differences in distributions of the quality of child attachment (secure vs. insecure-avoidant, -resistant, -disorganized) between both treatment modalities are calculated by a chi-square test of significant statistical independence. A power analysis for comparing COS and TAU with a power of 80% and the probability of making a Type I (α) error of 5%, with a medium effect (*W* = 0.3) suggested a recruited sample size of N = 80.

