### Secondary outcomes

a. To compare differences between COS and TAU on maternal sensitivity (MBQS, DIP) as continuous secondary outcome variables, a 2x2 analysis of covariance (ANCOVA), with repeated measurement (t0-t1) on one first factor, will be used. In these analyses, treatment modality will be treated as the second factor, maternal sensitivity as the dependent variable, and maternal psychopathology (BDI, SCL-90-R) and maternal parenting stress (PSI) as co-variables.

b. To compare differences between COS and TAU on maternal mentalization (RF, PRFQ-1) as continuous secondary outcome variables, a 2×2 analysis of covariance (ANCOVA), with repeated measurement (t0-t1) on one first factor, will be used. In these analyses, treatment modality is to be treated as the second factor, maternal mentalization as dependent variable, and again, maternal psychopathology (BDI, SCL-90-R) and maternal parenting stress (PSI) as co-variables.

c. Furthermore, in a multiple linear regression, the differences in maternal sensitivity and mentalization will be used to predict psychopathology and maternal stress (with treatment modality, differences in psychopathology, and differences in maternal distress as independent variables).

d. Before analyzing the proportions of mothers whose attachment representations change during the treatment and follow-up period in both treatment arms, we will separate those mothers with a positive shift in attachment representations [i.e., insecure (-dismissing, preoccupied, unresolved) to secure) from the mothers without such a shift or with a negative one ((i.e., secure to any of the others)]. For binary responses, a binary logistic regression will be used to compare proportions of mothers whose attachment representations (positive shift vs. no/negative shift) have been altered as a criterion variable, and treatment group (COS vs. TAU), differences of maternal psychopathology (BDI, SCL-90) as well as parenting stress (PSI) prior and after treatment as predictor variables.

e. To examine associations between changes of psychopathology (BDI, SCL-90) and changes in parenting stress (PSI) between pre- and post-assessment, a Pearson correlation analysis with the difference scores will be conducted.

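### Secondary analyses a and b treat the baseline score as an outcome instead of adjusting for it, which costs precision; to a smaller and uncertain degree, so does leaving the randomisation age stratum out of the primary test

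*Protocol article*

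**What the plan says.** **Randomisation.** The article (Randomization procedures and methods to minimize bias) stratifies by infant age, 4–6 against 7–9 months, and "separate random lists were created for each age group".

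**Primary outcome.** Differences in the proportion of securely attached children "between TAU and COS treatment arms will be estimated by a chi-square test of statistical significance". Age stratum is not mentioned there, nor in any of the listed analyses a to h. Item h is a logistic model of attachment security on treatment and several maternal variables; it also omits the stratum.

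**Secondary outcomes a and b.** Sensitivity (MBQS, DIP) and mentalization (RF, PRFQ-1) are each analysed by a 2x2 ANCOVA "with repeated measurement (t0-t1) on one first factor, will be used". Treatment is the second factor. The covariates are BDI, SCL-90-R and PSI; the baseline value of the outcome is not among them, because it is one of the two repeated values.

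**Sample size.** The power analysis "suggested a recruited sample size of N = 80". The Limitations section then says: "For practical reasons, we defined a sample size of N = 72", that is, 36 dyads per arm.

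**The concern.** Both parts concern efficiency, not bias.

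In a and b, the term that compares arms on improvement is treatment by time. With only two time points it is the same test as comparing mean change scores (within the covariates fitted). A change score subtracts the whole baseline value, whereas regression on baseline subtracts only the part that predicts follow-up. In a randomised trial the second is more precise whenever the baseline–follow-up correlation is below 1. These analyses carry secondary hypotheses i and ii, and with 36 dyads per arm the difference is material.

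For the primary outcome, stratified randomisation balances the arms on age. If age predicts attachment, this reduces the true variance of the difference between arms, but an unstratified chi-square still uses the larger pooled variance. It then rejects too rarely. If age does not predict attachment, nothing is lost.

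**Working it through.** **Inputs.** From the article: 36 per arm (Limitations); two age strata with separate lists; 1:1 allocation; alpha 5%, power 80% and w = 0.3 (Sample size and power). Assumed, because the article gives no figure: rho, the correlation between baseline and follow-up score (0.3 to 0.7); equal variances at the two times; a standardised effect of 0.5 on the secondary scores; two equal age strata; secure rates of 35% and 65%, which is w = 0.3 at a mean rate of 50%; a stratum difference of 0 to 30 percentage points. All tests are two-sided at 5%, before drop-out.

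**Step 1. The plan's own figure.** With 1 degree of freedom, N = (1.960 + 0.842)² / 0.3² = 87.2, so 88, not 80. Power is 76.5% at N = 80 and 72.1% at N = 72. That is a separate matter; here it shows only that precision is scarce.

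**Step 2. Secondary a and b.** Scale each score to SD 1.

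- Change score: variance = 1 + 1 − 2 rho = 2(1 − rho).
- Follow-up adjusted for baseline: residual variance = 1 − rho².
- Ratio = (1 − rho)(1 + rho) / [2(1 − rho)] = (1 + rho)/2.

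Power comes from the noncentral t with noncentrality 0.5 / [s × √(2/36)], where √(2/36) = 0.2357, s is the square root of the variance above, and the degrees of freedom are 70 (change) or 69 (adjusted).

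| rho | ratio | change: s, noncentrality, power | adjusted: s, noncentrality, power |
|---|---|---|---|
| 0.3 | 0.65 | 1.183, 1.793, 42% | 0.954, 2.224, 59% |
| 0.5 | 0.75 | 1.000, 2.121, 55% | 0.866, 2.449, 68% |
| 0.7 | 0.85 | 0.775, 2.739, 77% | 0.714, 2.970, 83% |

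A comparison of follow-up scores alone has s = 1 and power 55% at any rho. Below rho = 0.5, therefore, the planned test is less precise than ignoring baseline altogether.

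**Step 3. Primary outcome, variance.** Take a 50% secure rate overall and strata at 50% ± d/2. The average within-stratum variance is 0.25 − d²/4, while the chi-square uses 0.25. The ratio is 1 − d²: 1, 0.99, 0.96 and 0.91 for d = 0, 0.1, 0.2 and 0.3.

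**Step 4. Primary outcome, size and power at N = 72.** There are four cells of 18 children (arm by stratum), each binomial. All outcomes were enumerated, and the unstratified chi-square was compared with the Cochran-Mantel-Haenszel (CMH) test. For power, the rates are 35% ± d/2 and 65% ± d/2.

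| stratum difference | size, chi-square | size, CMH | power, chi-square | power, CMH | gain (points) |
|---|---|---|---|---|---|
| 0 | 4.5% | 4.5% | 72.0% | 72.0% | 0 |
| 10 points | 4.4% | 4.5% | 72.1% | 72.4% | 0.3 |
| 20 points | 4.1% | 4.6% | 72.4% | 74.1% | 1.7 |
| 30 points | 3.6% | 4.9% | 72.9% | 77.6% | 4.7 |

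The chi-square's size is already 4.5% with no stratum effect, because the counts are discrete. Only the fall below 4.5% is due to omitting the stratum.

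**The case against.** The strongest reply is that the article describes valid analyses and that this point expresses a preference among them. In part this stands. Change-score and repeated-measures analyses are unbiased under randomisation, and leaving out the stratum can only lower the size that the chi-square would otherwise have.

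On the primary outcome the reply goes further. Nothing in the article says that age at entry predicts attachment, and all children are assessed at 16–18 months. A reader might infer that precision is certainly being lost there. The documents do not support that: the gain is nil without a stratum effect and small up to a 20-point difference. It also shifts with the exact number analysed. At a 20-point difference it is about 0.2 points at N = 80 and 3.4 at N = 68.

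On a and b, the ratio (1 + rho)/2 assumes equal variances, and rho should be read as the correlation remaining after BDI, SCL-90-R and PSI. This changes the size of the loss. With equal variances its direction is the same for every rho below 1.

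Two other stronger readings fail:

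- A reader might infer that the treatment main effect will be tested, which would dilute the effect by averaging in the pre-treatment score. The article does not name the term, but hypotheses i and ii speak of an increase relative to TAU, which is treatment by time.
- A reader might infer that further baseline predictors in the primary model would be worth a definite number of dyads. The Strange Situation is not done at baseline, and the article gives no association between any baseline measure and attachment.

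Finally, a chi-square test does not itself estimate a difference. The choice of effect measure and interval may stand in an analysis plan that is not shown, so this is not counted as a fault.

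**Conclusion.** The point holds as one of efficiency. Its main weight is on secondary analyses a and b. Under the assumptions stated, baseline-adjusted analysis needs 65% to 85% of the change-score sample for rho of 0.3 to 0.7. At 36 per arm and an effect of 0.5 SD it raises power by about 17, 12 and 6 points. The loss follows from the model the article names, so it does not depend on detail left to another document.

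The primary part is minor and conditional: 0 to about 5 points of power at N = 72, depending on a stratum effect that the article does not give. The planned chi-square remains valid, and no conclusion about bias follows in either part.

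**What to change.** **Secondary a and b.** Replace the repeated-measures model by an ANCOVA of the follow-up score on treatment, the same score at baseline and the age stratum. Report the adjusted mean difference with its 95% confidence interval.

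**Primary outcome.** Replace the unstratified chi-square by a CMH test stratified by infant age, or by a logistic model with treatment and age stratum. Report the stratum-adjusted risk difference with its 95% confidence interval. No further covariates are needed for this point.

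**Cost.** Wording only. The age stratum is known from randomisation, and mini-MBQS, DIP, RF and PRFQ-1 are all measured at baseline and follow-up (Table 1). The article says that follow-up is continuing, so the change can be fixed before outcomes are compared by arm.
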